#### Medium Self-Management Support Intervention

The medium self-management support intervention consists only of the online videos and e-bulletins as described above.

#### Minor Self-Management Support Intervention

The minor self-management support intervention consists only of the e-bulletins, the same as those in the major and medium support interventions.

### Measurement Procedures

Measurements will be performed in the RCT at 3 time points: baseline assessment (T0), which is just before the family care intervention arms start; the assessment 6 weeks after the baseline (T1); and the assessment 12 weeks after the baseline (T2). Measurements will be based on self-reporting by the family caregiver and will be administered through the Internet. Up to 2 email reminders will be sent (if necessary) 1 and 2 weeks after the measurement time point to remind participants to complete the questionnaires.

### Primary Outcome

The primary outcome in the RCT is self-efficacy, measured by the Trust in Own Abilities (TOA) instrument, a Dutch language questionnaire to be completed by family caregivers of the person with dementia [23]. The questionnaire has been used before to measure self-efficacy in caregivers of people with dementia living at home [24]. The TOA contains 32 items (alpha .97) divided into 3 subscales: resilience (15 items, alpha .94), solution orientation (8 items, alpha .90), and proactive competence (9 items, alpha .81). Items are measured on a 5-point Likert scale, ranging from 0 (not at all) to 4 (very good). A higher score is associated with higher perceived competence in taking care of the person with dementia [24].

### Secondary Outcomes

The secondary outcome will be the presence and number of behavior and mood problems, assessed with the Dutch version of the Revised Memory and Behavioral Problem Checklist (RMBPC) [25,26]. Family caregivers have to rate the frequency of the occurrence of a specific behavior or mood problem on a scale from 0 (never) to 4 (always) where 1 is seldom, 2 regularly, and 3 is often. The total number of behavior and mood problems (0 to 24) will be calculated as well as the mean overall score. The RMBPC can be divided into scales for depression (9 items), disruptive behavior (8 items), and memory-related problems (7 items).

Another secondary outcome is the positive and negative aspects of the family relationship between the family caregiver and the person with dementia and they will be measured by the Dyadic Relationship Scale (DRS). The family caregiver version includes 11 items in 2 subscales: dyadic strain and positive dyadic interaction. Family caregivers have to rate the quality of the relationship using 4 answer categories: 1 (strongly disagree), 2 (disagree), 3 (agree), and 4 (strongly agree) [27].

### Analyses of Effects

The quantitative data from the RCT will be analyzed using SPSS software (Statistics 22). Baseline characteristics will be described for each arm using proportions for dichotomous variables and means (SD) or medians (IQR) for continuous variables. In the primary analysis, primary and secondary outcomes will be compared between the 3 different groups using mixed-models analysis. All mixed model analysis will be adjusted for baseline differences between the groups.

All randomized caregivers who completed the follow-up will be included in this analysis (modified intention-to-treat). The first 9 caregivers, who are in the learning-curve block, will not be included in the primary analysis. We will use sensitivity analyses to evaluate the effect of missing data and of the prior inclusion of key baseline variables.

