### Power Calculation and Sample

We hypothesize that (1) both the major and medium intervention arms improve the self-efficacy as compared to the minor intervention arm; and (2) the major intervention arm gives better results for self-efficacy compared to the medium intervention arm. Considering a difference of 0.8 standard deviation units between the groups and assuming a significance level of .05, a power of 80%, and a correlation of .6 between the 2 repeated measures, 20 participants are needed per group. Taking into account a drop out percentage of 20%, we will include 24 participants per group.

In this study, providing self-management support through email is a relatively new task for the specialized nurses involved, with possible learning effects during the study. To take this into account, 1 extra block of 9 participants will be added to allow for a brief learning curve. Hence, in total 81 family caregivers of persons with dementia will be included.

The participants will be family caregivers of people with dementia who meet the following inclusion criteria: (1) the family caregiver is a relative of a person diagnosed with dementia (all types of dementia are eligible, with no restriction on the severity of the dementia); (2) the family caregiver must have contact with the person with dementia at least once a week; (3) the family caregiver's relative with dementia has to live at home (not in a care institution); (4) the family caregiver has access to the Internet and has basic skills in using the Internet and email; (5) the family caregiver has to be aged at least 18 years of age; and (6) the family caregiver is able to read and write Dutch.

To recruit family caregivers for our study, we will use several channels. The panel of the Dutch Alzheimer Society (in which more than 3000 informal caregivers participate) will be sent an email with an open call. Open calls will also be posted on the online forum of the Dutch Alzheimer Society (with 7000 monthly visitors), on the Dementie Nederlands website, and on the social media accounts (Facebook/Twitter) of the Dutch Alzheimer Society.

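### The primary analysis set depends on completing follow-up, does not say which follow-up, and can bias the comparison if arm-specific dropout is related to outcome

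*Protocol article*

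**What the plan says.** In the protocol article, section Analyses of Effects, the comparison is defined thus: "primary and secondary outcomes will be compared between the 3 different groups using mixed-models analysis". The next paragraph fixes who enters it: "All randomized caregivers who completed the follow-up will be included in this analysis (modified intention-to-treat". A second, separate exclusion follows: "The first 9 caregivers, who are in the learning-curve block, will not be included in the primary analysis". On adjustment the article says "All mixed model analysis will be adjusted for baseline differences between the groups", and on missing data "We will use sensitivity analyses to evaluate the effect of missing data and of the prior inclusion of key baseline variables".

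The section Power Calculation and Sample expects losses: "Taking into account a drop out percentage of 20%, we will include 24 participants per group". Measurement Procedures sets two follow-ups, T1 at 6 weeks and T2 at 12 weeks. No section states that a caregiver with only one of the two stays in the primary analysis.

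**The concern.** The set is a stated rule, not a detail left to another document, and it conditions on a post-randomisation event. Randomisation balances all allocated caregivers, not those who go on to finish. The arms differ in what they ask and offer (nurse emails, videos and bulletins against bulletins alone), participants are not blinded, and the outcome is self-reported. Dropout that differs by arm and is related to self-efficacy is therefore possible.

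The rule also sits awkwardly with the chosen model. A likelihood-based mixed model can use a T1 score from someone without T2 and is valid under missing at random, an advantage that a completers-only set gives up. Because completion is not tied to T1, T2 or both, membership of the primary set could also be settled after the data are seen. At stake are the size of the headline contrast, its type I error, and some precision in a trial with about 20 evaluable caregivers per arm.

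**Working it through.** **Inputs from the article.** 24 per group, three groups, 20% dropout, 0.8 SD, significance level .05, 80% power, correlation .6 (Power Calculation and Sample); T0, T1 and T2 (Measurement Procedures).

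**Assumed, not in the article.** A two-sided test; correlation .6 between every pair of time points; all loss after T1 unless stated; how dropout splits by arm; and a logit slope linking lower scores to dropout.

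**1. The plan's own figure.** n per group = 2 × (1.960 + 0.842)² / 0.8² × (1 + 0.6)/2 = 24.53 × 0.8 = 19.6, so 20. A change-score factor, 2 × (1 − 0.6) = 0.8, gives the same. Then 20 × 1.2 = 24 (20/0.8 would give 25), and 3 × 24 + 9 = 81. The sample size is reproduced and is not in dispute.

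**2. Who is affected.** Outside the learning-curve block: 3 × 24 = 72. Expected non-completers: 0.2 × 72 = 14.4. Completers: 57.6, or 24 × 0.8 = 19.2 per arm.

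**3. Bias in large samples.** 300,000 per arm, true effect 0.8 SD, T2 contrast adjusted for T0, slope 1 per SD. The first rate belongs to the arm whose advantage is estimated.

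| Dropout depends on | Rates | Completers only | All available data |
|---|---|---|---|
| nothing (random) | 30% vs 10% | about 0 | about 0 |
| T0 only | 30% vs 10% | about 0 | about 0 |
| T1 (observed) | 20% vs 20% | about 0 | about 0 |
| T1 (observed) | 30% vs 10% | +0.04 SD | about 0 |
| T1 (observed) | 40% vs 10% | +0.06 SD | about 0 |
| T2 (unobserved) | 20% vs 20% | about 0 | about 0 |
| T2 (unobserved) | 30% vs 10% | +0.11 SD | +0.10 SD |
| T2 (unobserved) | 40% vs 10% | +0.16 SD | +0.14 SD |

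Swapping the rates to 10% vs 30% reverses the sign, so the direction depends on which arm loses more.

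**4. Bias and type I error at trial size.** 24 per arm, no true effect, dropout driven by T1, completers analysed with adjustment for T0, 6,000 to 12,000 trials per run. Ranges span separate runs.

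| Slope per SD | Rates | Outcome | Bias | Type I error |
|---|---|---|---|---|
| 1.5 | 35% vs 5% | mean of T1 and T2 | +0.14 to +0.16 SD | 9.8% to 10.0% |
| 1.5 | 30% vs 10% | mean of T1 and T2 | +0.09 to +0.10 SD | 7.0% to 7.7% |
| 1.5 | 30% vs 10% | T2 | +0.06 SD | 5.3% |
| 1 | 30% vs 10% | T2 | +0.04 SD | 5.3% |
| 1 | 25% vs 15% | mean of T1 and T2 | +0.04 SD | 5.1% |
| 1 | 25% vs 15% | T2 | +0.02 SD | 5.0% |

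In the first two rows, a likelihood analysis of all available data has bias of about 0. With equal dropout, completers-only is unbiased but its standard error is roughly 2% to 7% larger. In a large-sample run of the second row's setting, moving half the loss to before T1, dependent on T0, cuts the bias from +0.10 to +0.06 SD (+0.03 SD for T2).

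**5. Against the design effect.** 0.02/0.8 = 2.5% and 0.16/0.8 = 20%.

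**The case against.** The article is open about the restriction: it calls the set modified intention-to-treat in the sentence that imposes it, plans sensitivity analyses for missing data, and sizes the trial for about 20 analysed per group after dropout, which fits a completer set. The detail of those sensitivity analyses may sit in a document not shown and is not faulted here. All of this stands, but none of it changes the set on which the headline estimate rests.

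A reader might infer three stronger claims that the article does not support:

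- **Unequal dropout by itself biases the result, or the randomised comparison is lost outright.** It does not follow. With 30% vs 10% loss the bias is about 0 when loss is random or depends only on the adjusted baseline.
- **The plan certainly discards T1 scores already collected.** That is the more literal reading, but the article does not say which follow-up must be completed. If one score suffices, only caregivers with T0 alone are left out. They carry almost no information on the contrast, and the T1-driven bias above does not arise.
- **The major arm will lose more caregivers and so look too good.** The article gives no dropout by arm. Nurse contact could equally improve retention, and the sign would then reverse.

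The larger simulated figures also rest on the less favourable assumptions. Most milder T1-driven settings give small bias and near-nominal type I error.

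**Conclusion.** The point holds in conditional form. The primary set is defined by completing follow-up, the required follow-up is not specified, and no other section keeps partial completers. The estimate can be biased when dropout differs by arm and is related to follow-up scores beyond baseline. The bias is then about 0.02 to 0.16 SD across the assumed scenarios, with type I error from about 5% to 10% in the T1-driven null simulations. Otherwise it is about 0. Only the 20% overall dropout, the .6 correlation and the 0.8 SD effect come from the article; the splits, slopes and timing are assumptions.

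Using all available data removes the bias when dropout depends on observed scores. It helps little when dropout depends on unobserved T2 scores (+0.10 SD remains of +0.11 SD at 30% vs 10%). Severity: should-fix.

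**What to change.** Replace the sentence that defines the analysis set with:

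> The primary analysis includes all randomised caregivers outside the learning-curve block, in the arm to which they were allocated; every available T1 and T2 score enters the likelihood-based mixed model, whether or not the other follow-up was completed. The completers-only analysis is a sensitivity analysis.

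The reference to the learning-curve block is needed because the article excludes that block separately, and a bare reference to all randomised caregivers would bring it back. Caregivers with T0 only can be kept by modelling T0 as a response with a common baseline mean.

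Add at least one not-missing-at-random scenario to the missing-data sensitivity analyses already planned.

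Cost: one sentence and one further sensitivity scenario. The data, the software and the sample size stay the same. The change should be recorded before outcomes are compared by arm.

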#### Major Self-Management Support Intervention

The major intervention arm consists of the following elements: (1) 3 personal email contacts with a nurse specialized in dementia care, (2) provision of online videos about how to manage behavior changes in a relative with dementia and to improve your self-efficacy in managing with this behavior, and (3) provision of e-bulletins with practical information about different types of behavior changes and how to manage them.

The personal email contacts will be handled by a nurse with a Bachelor’s or Master’s qualification in nursing and with follow-up training in dementia care. In the email contact, the nurse will support the family caregiver in managing behavior changes. The nurse will also give feedback on assignments and will give feedback on the plan that the family caregiver came up with in the assignments. The nurse will tailor their support to the personal needs and questions of the family caregiver, while guided by an intervention protocol developed by project group members ([name], [name], [name], [name]), in consultation with the nurses who had to use the intervention protocol. The number of email contacts was discussed and agreed with experts in dementia care who have experience with online support. Three email contacts are thought to be sufficient and feasible.

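### The learning-curve exclusion removes caregivers from all three arms, although its reason concerns only the major arm, so the medium-minor contrast gives up usable data

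*Protocol article*

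**What the plan says.** The protocol article, under Power Calculation and Sample, sizes the trial at 24 per group and then adds nine more: "1 extra block of 9 participants will be added to allow for a brief learning curve". The reason is that "providing self-management support through email is a relatively new task for the specialized nurses involved, with possible learning effects during the study". The total is 81.

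Under Analyses of Effects the rule becomes: "The first 9 caregivers, who are in the learning-curve block, will not be included in the primary analysis". It makes no distinction between arms. The sensitivity analyses listed there concern missing data and key baseline variables; none brings the nine back.

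The descriptions of the three arms place email contact with a nurse in the major arm only. The medium arm receives videos and e-bulletins, and the minor arm e-bulletins alone. Design and Randomization gives block sizes of 6 and 9. The first hypothesis, under Power Calculation and Sample, includes an advantage of medium over minor.

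**The concern.** The exclusion is wider than its reason. A nurse's inexperience with email support can affect the outcome only of caregivers who write to a nurse. Caregivers in the medium and minor arms received the same material in the learning block as those who entered later, so the stated reason gives no ground for leaving them out of a comparison between those two arms.

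Two things are at stake. The medium-minor contrast, which the trial sets out to test, is estimated from fewer caregivers than were randomised to it under identical conditions. And because no listed analysis includes the nine, a reader cannot tell whether leaving them out altered any of the three comparisons.

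**Working it through.** **Inputs, all from Power Calculation and Sample unless noted**

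- Effect: "Considering a difference of 0.8 standard deviation units between the groups".
- Error rates and correlation: "assuming a significance level of .05, a power of 80%, and a correlation of .6 between the 2 repeated measures". The article does not say one- or two-sided; two-sided is assumed here.
- Group size: "20 participants are needed per group", then "Taking into account a drop out percentage of 20%, we will include 24 participants per group".
- Learning block: nine caregivers. A 1:1:1 split is inferred from the equal group sizes and from a block size of 9 over three arms.

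**Step 1: reproduce the plan's figure.** With correlation 0.6, the variance factor is 0.8 both for the mean of two measures, (1 + 0.6)/2, and for a change score, 2(1 − 0.6). Then

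n per group = 2 × 0.8 × (1.960 + 0.842)² / 0.8² = 19.6, rounded up to 20.

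This matches. The total also matches: 3 × 24 + 9 = 81.

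**Step 2: who is excluded.** 9 / 3 = 3 per arm, so three caregivers have a nurse and six do not. Without the block, each arm has 24; with it, 27. The share forgone in each of the medium and minor arms is 3/27 = 11%.

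**Step 3: numbers analysed after 20% dropout.** 24 × 0.8 = 19.2 per arm, or 27 × 0.8 = 21.6 per arm.

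**Step 4: power for medium versus minor**, as Φ( 0.8 / √(0.8 × 2/n) − 1.960 ):

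| Set used | n per arm | Standardised difference | Power |
|---|---|---|---|
| Plan's target | 20 | 2.828 | 80.7% |
| Block excluded | 19.2 | 2.771 | 79.1% |
| Block included | 21.6 | 2.939 | 83.6% |

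The gain is 4.5 percentage points. In terms of precision, √(21.6/19.2) = 1.06, so the interval is about 6% wider with the block excluded.

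**Step 5: dependence on the variance factor.** If adjusting for baseline gives a factor of 1 − 0.6² = 0.64, the same formula gives 87.3% at 19.2 per arm and 90.8% at 21.6, a gain of 3.5 points. The normal approximation is slightly generous: at 20 per arm with factor 0.8, a t-based calculation gives 78.7% rather than 80.7%. The levels of power therefore depend on method, but the gain stays at a few points.

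**The case against.** The strongest defence is that the exclusion is a sound design rule. It was fixed in advance, does not depend on outcome and removes an intact randomised block, so the arms stay balanced and concurrent and one population serves the three-group model. Dropping only the three major-arm caregivers would leave early medium and minor caregivers without concurrent major-arm counterparts. This stands for the two major-arm contrasts. It does not reach medium versus minor, where the six were randomised alongside each other, three per arm.

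A second defence is that nothing planned is lost. The nine were added to the 72, so excluding them leaves 24 per arm. This also stands. The 79.1% falls just short of 80% because 24 is 20 × 1.2, which after 20% dropout leaves 19.2; the exclusion is not the cause. The 83.6% is power that the trial was not sized to have, from participants whom it enrols anyway. A reader might infer that the rule damages the planned sample or biases the result; the article supports neither.

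A reader might also infer that some nurses do their learning inside the analysed sample, because three practice cases are shared among them. The article refers to nurses in the plural ("in consultation with the nurses who had to use the intervention protocol") but gives neither their number nor how caregivers were assigned to them. With two or three nurses, each could have had a case, so this is conjecture.

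Finally, a reader might conclude that the analysis ignores clustering of caregivers by nurse. The article names a mixed model without giving its random effects, a detail that a condensed article may leave to the full protocol or analysis plan. What can be said is that the stated sample-size inputs contain no allowance for nurse clustering. How much that matters depends on a number of nurses and an intraclass correlation that the document does not give.

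**Conclusion.** The point holds as one of efficiency and transparency. The reason for the exclusion concerns one arm and the rule acts on three. For the major-arm contrasts the rule is defensible as written. For medium versus minor it forgoes three concurrent caregivers per arm, worth about 4.5 points of power on the plan's inputs (79.1% against 83.6%), and no listed analysis shows what the exclusion does to any of the results. The size rests on a balanced block of nine, 20% dropout in both arms, a two-sided 5% test and the variance factor of 0.8 that reproduces the plan's 20 per group.

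**What to change.** 1. Estimate the medium-minor contrast from all 54 caregivers randomised to those arms (27 + 27), under the same follow-up rule as the rest of the analysis.
2. Keep the whole-block exclusion for major versus medium and major versus minor.
3. Report the same model on all 81 as a sensitivity analysis, beside the primary results.

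The cost is a few extra model runs on data that the trial collects anyway. The drawback is that the three contrasts rest on slightly different sets of participants, which the report should state with the number in each. Since the article gives data collection as complete in August 2017, the date of this decision should be recorded, and the analyses labelled post hoc if it followed any comparison of the arms.

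A model with a nurse effect in the major arm is optional. With only a few nurses, the variance between them would be poorly estimated.

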### Process Evaluation

Alongside the RCT, a process evaluation will be conducted. Mixed-methods and sources will be used for this. Firstly, evaluation questions will be included in the T2 survey questionnaire (12 weeks after the baseline). The number of evaluation questions varies between 5 and 11 depending on which of the 3 intervention arms the family caregiver is in. The evaluation questions are based on earlier research about the perceived feasibility and usability of interventions and satisfaction with the interventions [28,29].

Secondly, semi-structured interviews will be conducted with a purposive sample of about 15 participant family caregivers (5 participants in each intervention arm). The participants will be purposively recruited to achieve a spread in the intervention arms and background characteristics (eg, sex, age, and living with or separately from the relative with dementia). Topics will include family caregivers' satisfaction with and the perceived feasibility and usability of the self-management support interventions. The interviews will be conducted by telephone by 1 of the members of the research team ([name]) and will be audio-recorded.

Thirdly, usability in the sense of actual usage of the different elements of the online self-management support intervention will be measured by analyzing the clicks on links and how long the family caregivers spent watching the videos, divided into the following categories: (1) started video, (2) played video (25%), (3) played video (50%), (4) played video (75%), and (5) completed video. These data will be collected with Google Analytics. All participating family caregivers will be given a unique code that is known only by the research team.

To collect data on actual use of the personal email contacts, nurses will be asked to complete a registration form on the number of personal email contacts per family caregiver and time spent on giving feedback to the family caregiver.

Fourthly, the content of the email contacts between the family caregivers and the nurses will be analyzed qualitatively. The email contacts will be analyzed from 3 angles: with a focus on nurses’ questions and responses, with a focus on family caregivers’ questions and responses, and with a focus on the interactions between the two. The focus on the nurses will be on how they delivered the self-management support as defined by the intervention protocol based on the “5A model” (assess, advise, agree, assist, and arrange). The responses by the family caregivers in the email contacts will be analyzed to get information on the uptake of the intervention and how they integrated the personalized advice from the nurse in their daily lives.

The data from the structured evaluation questions in the T2 survey questionnaire, data on actual usage from Google Analytics, and registration data on the number of personal email contacts will be analyzed descriptively using SPSS software. The semi-open interviews and the content of the email contacts will be analyzed qualitatively using the principles of thematic analyses [30]. This qualitative method was chosen because it is a useful and flexible method for identifying relevant themes within qualitative data. It consists of the following steps: (1) familiarizing yourself with the data, (2) generating initial codes, (3) searching for themes, (4) reviewing themes, (5) defining and naming themes, and (6) reporting [30]. The interview transcripts will be analyzed by 2 researchers ([name] and [name]) independently. Coding and interpretation of the codes will be discussed by the researchers until consensus is reached. In addition, other authors will comment on the interim analyses of the interviews.

